### Secondary outcome measurements

Secondary *patient outcomes* are well-being, activities of daily living (ADL), and quality of life for both elderly participants and caregivers.

*Well-being* will be measured using the Groningen Well-being Indicator (GWI). This questionnaire measures eight domains of well-being regarding daily experiences: enjoying eating and drinking, sleeping and resting well, having good relationships and contacts, being active, managing yourself, being yourself, feeling healthy in body and mind, and living pleasantly. Respondents have to indicate whether the domains are important to them and, if so, whether they are satisfied with them (as yet unpublished).

*Activities of daily living (ADL)* will be measured using the modified Katz ADL index. This index consists of fifteen items and measures eight physical and seven instrumental ADL. It measures ADL performance by counting the number of disabilities, with a higher score indicating worse functional status (ranging from 0–15) [55].

*Quality of life* of both elderly participants and caregivers will be assessed using two items which are formulated according to the RAND-36 formulation [56]. The first item measures the self-rated quality of life while the second item compares the current self-rated quality of life with quality of life a year earlier.

Secondary outcomes for *quality of care* are the impact of interventions as offered to elderly participants and the perceived chronic illness care from the perspective of the professionals.

*Impact of interventions* will be examined within the intervention group using GAS [57]. GAS is an individualized measure for evaluating the impact of interventions as recorded in the care and support plans of the frail participants and participants with complex care needs.

*Perceived chronic illness care* will be examined within the intervention group using the Assessment of Chronic Illness Care (ACIC) [58]. The ACIC is a professional self-report questionnaire that reflects on all elements of the CCM and evaluates – from the professionals’ perspective – the degree to which integrated care is realized. For this study, the English ACIC version was translated into Dutch using forward and backward translation [54] and modified for the targeted population by rephrasing items.

Secondary outcomes regarding the *cost analysis* will be cost effectiveness, calculated using self-report questionnaires that assess complexity of care needs, frailty, and functional status, in combination with the MDS-e, and – if possible – in combination with data collected from databases of health insurers and municipalities.

### Randomization

Figure 2 shows the procedure for random assignment to either the intervention or the control group. After stratification, a balancing procedure will be employed per stratum in order to achieve equal distributions of those characteristics that potentially affect intervention outcomes [59]. The balancing criteria will be age, sex, complexity of care needs, frailty, living situation, number of chronic conditions, whether or not receiving homecare, and whether or not receiving help with filling out the questionnaires. This balancing procedure will be performed within each GP practice.

**Figure 2 F2:**
[figure not shown]
The Embrace study flowchart.

### Statistical analysis

Descriptive statistics will be used to assess differences between intervention and control groups concerning basic characteristics and confounding variables.

Analyses of the effects regarding primary and secondary outcomes will be executed using the “intention-to-treat principle” [60]. The first analyses will focus on the differences between intervention and control groups after intervention, on the level of the sample and on the level of the strata, with respect to the primary and secondary outcomes. T-tests or (M)ANOVA will be used for continuous variables, Chi square tests, the Wilcoxon tests, and difference of proportions tests for discrete variables. Analysis for change in caregiver burden will focus on the differences between baseline and follow-up measurements by means of Wilcoxon tests, taking into account the duration of support in months. Clinical relevance of the effects will be estimated by Cohen’s effect sizes for statistically significant group differences (p < 0.05).

The incremental cost-effectiveness ratio will be calculated as total costs per QALY [61], and total costs per patient outcome measurement. Bootstrapping will be used to determine the confidence interval. Discounting will initially not be applied considering the limited follow-up period.

For calculation of the GAS, the method proposed by Rockwood [62] will be applied. The first step in this method is to relate the separate problem target scores to the achieved end scores. Next, three specific analyses are performed: 1) calculation of each individual problem score, 2) calculation of overall problem score for each patient, and 3) calculation of the sample score. Finally, the standardized GAS score is used to measure the extent to which the goals were achieved.

The psychometric properties of the PACIC [51] and PIH [53] will be analyzed separately, since these measurements were translated and modified for the current study. For the psychometric evaluation, we will employ confirmatory factor analysis and will estimate the reliability by calculating internal consistency. Criterion validity will be estimated with known-groups comparisons.

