Promotion of healthy ageing for all elderly people is essential in order to prevent disabilities and long-term care needs and to reduce service use in the long run [35]. Furthermore, since the health status of elderly individuals changes frequently and dramatically, those using care today may not use it next year, and vice versa. Consequently, an effective community-based integrated elderly care model should include all elderly people in that community, including the robust elderly [36,37].

To provide a suitable level of care and support for all elderly people in a population, the CCM can be combined with the Kaiser Permanente (KP) Triangle, a population management model for service delivery [19]. The KP Triangle distinguishes three levels with corresponding intervention strategies, based on the distribution of risk for health care needs across a population. At the first level, self-management support is offered to patients at a relatively low risk for health care needs. Patients at the second level have increased levels of risk for complex care needs and receive disease management or care management. The third level consists of high complexity patients, who receive intensive case management. Preventive care is provided at all three levels [17,38].

The aim of the present study is to evaluate the effectiveness of “Embrace” ("SamenOud" in Dutch), a novel population-based integrated elderly care model. Embrace combines the four interacting CCM key elements within the context of the community and health care system with stratification of community-living elderly people in terms of KP-based risk levels. Health outcomes for elderly people and their caregivers, as well as effects on quality of care, service use, and costs will be examined. The present paper will describe the design of the study.

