### Study population

Recruitment of the participants will be performed in two steps. First, all general practitioners (GPs) working in the three municipalities will be informed about the study and their consent to participate in the study will be requested. Second, patients from the participating GPs, aged 75 years and older and living at home or in a home for the elderly, are eligible for inclusion in the study and will be invited to participate. Exclusion criteria at baseline are long-term stay in a nursing home, receiving an alternative type of integrated care, or participating in another research study.

Eligible patients will receive a letter from their GP with general information about the intervention and the study performed by the university. One week later, patients will receive a written informed consent form accompanied by questionnaires for baseline measurement (T0). Patients are free to ask for support in filling out the questionnaire, either from family, friends, or from a volunteer available via the project helpdesk. Two and a half weeks later, a reminder will be sent to those patients who have not returned the questionnaire. A further one and a half weeks later, follow-up by telephone will start with respect to the persistent non-respondents. Finally, after inclusion and randomization, participants will be informed by letter about assignment to the intervention or control groups.

Informal caregivers of participants in the intervention group are also eligible for participation in the study. An informal caregiver is defined as a person who is structurally providing voluntary and unpaid care to someone in his/her family, household, or social network with physical, mental, or psychiatric disabilities. During the intervention, caregivers in the intervention group will be invited to participate in the study only after the elderly participant has agreed to their involvement in the study. Caregivers who are willing to participate will receive information about the intervention and study, an informed consent form, and a questionnaire.

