### Data collection

Data will be collected with 1) self-report questionnaires for elderly people and self-report questionnaires for professionals before the intervention (T0) and after twelve months (T1), 2) self-report questionnaires for caregivers during the intervention and at T1, 3) from the EERS, and 4) from the financial records of the health insurance company and municipalities involved after finishing the intervention period [45].

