### Primary outcome measurements

The primary *patient outcomes* are complexity of care needs, frailty, health status, and self-management ability. The primary caregiver outcome is caregiver burden.

*Complexity of care needs* will be measured using the IM-E-SA. The IM-E-SA measures case complexity with 22 items, divided over four domains: biological, psychological, and social needs, and health care. These domains are approached from three different time perspectives: history, current state, and prognosis [39]. The total score may range from 0 to 60, with a higher score reflecting a higher level of complexity [46].

*Frailty* will be measured using the GFI self-report version. The GFI assesses frailty in the physical, social, cognitive, and psychological domain with fifteen items. The total score may range from 0 to 15, with a higher score indicating a higher level of frailty [40,47].

*Health status* will be measured using the EuroQol-5D (EQ-5D). The EQ-5D is a short self-report questionnaire which measures five dimensions of health by five items on a 3-point scale, ranging from no problems to severe problems: mobility, self-care, usual activities, pain/discomfort, and anxiety/depression. It also includes a Visual Analogue Scale (VAS) to rate the individual’s current health-related quality of life state on a scale ranging from 0 (worst imaginable health state) to 100 (best imaginable health state) [48].

*Self-management ability* will be assessed using the Self-Management Ability Scale (SMAS-30). It contains 30 items which are scored on 5- and 6-point Likert scales. It has six subscales: taking initiatives, self-efficacy beliefs, investment behavior, positive frame of mind, multi-functionality of resources, and variety in resources. The total SMAS score is the average of the six subscale scores, with a higher score indicating better self-management abilities (0–100) [49].

*Caregiver burden* will be evaluated using the Caregiver Strain Index (CSI) which measures both objective and subjective areas of strain: employment, financial, physical, and social areas, and time. It contains thirteen items which are scored on a dichotomous rating scale, with four to six positive responses indicating increased burden and seven or more positive responses indicating a high level of strain [50].

The primary outcomes for *quality of care* are the perceived chronic illness care from the perspective of the participants and their self-management knowledge and behavior.

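### Caregiver burden is a primary outcome under the effectiveness aim, but it is measured only in intervention-group caregivers and first during the intervention, so its before-after test cannot show an effect of Embrace

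*Protocol article*

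**What the plan says.** The Background section of the protocol article states the aim as evaluating the effectiveness of Embrace and continues: "Health outcomes for elderly people and their caregivers, as well as effects on quality of care, service use, and costs will be examined". Under Primary outcome measurements: "The primary caregiver outcome is caregiver burden". Table 2 lists CSI as a primary and quality of life as a secondary caregiver outcome.

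On who is enrolled and when, Study population says "Informal caregivers of participants in the intervention group are also eligible for participation in the study", and then "During the intervention, caregivers in the intervention group will be invited to participate in the study only after the elderly participant has agreed". Data collection sets two schedules side by side. One is "self-report questionnaires for elderly people and self-report questionnaires for professionals before the intervention (T0) and after twelve months (T1"). The other is "self-report questionnaires for caregivers during the intervention and at T1".

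Statistical analysis first says that primary and secondary outcomes are compared between intervention and control groups after the intervention, under intention to treat. For caregivers it then says "Analysis for change in caregiver burden will focus on the differences between baseline and follow-up measurements by means of Wilcoxon tests". The sentence closes with a promise to allow for how long support lasted, without naming a method.

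Table 2 carries a footnote for measures taken in the intervention group. It is attached to goal attainment scaling and to the professionals' assessment of chronic illness care, but not to CSI or caregiver quality of life. The limitations in the Discussion cover follow-up length, selection bias and contamination. They do not mention caregivers.

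**The concern.** A reader who sees CSI in the primary column of Table 2, without the intervention-group footnote, in a randomised trial whose general analysis compares the arms, will take it as a randomised outcome. It is not. No control caregivers are enrolled, so randomisation contributes nothing to this outcome. The value called baseline is also not a pre-intervention value.

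What is at stake is the meaning of a p-value. The article itself says that elderly people's health changes often and sharply, and that chronic conditions fluctuate. Caregiver burden can plausibly move with the condition of the person cared for. A significant before-after change could then be read as a primary effect of Embrace when it is background change, and a true effect could be hidden by background worsening. Any change in burden before the first questionnaire is not in the comparison at all.

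**Working it through.** **1. The statements set side by side (protocol article)**

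| Element | Elderly participants | Caregivers |
|---|---|---|
| Arms enrolled | Intervention and control | Intervention only |
| First measurement | Before the intervention (T0) | During the intervention |
| Last measurement | Twelve months (T1) | T1 |
| Analysis stated | Between arms after the intervention | First versus last measurement, Wilcoxon |
| Role | Primary and secondary outcomes | CSI primary, quality of life secondary |

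Two things follow without arithmetic. The between-arm analysis stated for primary outcomes cannot be carried out for CSI. The word baseline in the caregiver analysis does not refer to T0.

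**2. What the before-after difference contains**

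Suppose a caregiver is first measured at time t after the start. The observed change is then

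CSI(T1) − CSI(t) = effect of Embrace between t and T1 + background change between t and T1.

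In a two-arm comparison the background term would be expected to cancel. Here nothing estimates it. Any effect of Embrace before t is already in CSI(t) and is subtracted out. The article does not give t.

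**3. How far background change can move the test (illustration only)**

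The article has no caregiver sample size, CSI mean, SD or expected change. Its only sample-size calculation is for the EQ-5D visual analogue scale in elderly participants and does not bear on this point. All inputs below are therefore assumptions, except the 0-13 range, which follows from CSI's thirteen dichotomous items: mean 5, SD 3, within-person correlation 0.6, scores rounded and held to 0-13, no effect of Embrace, a two-sided Wilcoxon signed-rank test at 0.05, and 2,000 simulated trials per cell.

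Share of simulated trials with p < 0.05:

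| Caregivers | No drift | −0.5 point | +0.5 point | −1 point | +1 point |
|---|---|---|---|---|---|
| 50 | 4.6% | 25.4% | 23.8% | 68.6% | 70.4% |
| 100 | 5.1% | 41.6% | 42.7% | 94.6% | 94.1% |
| 200 | 4.4% | 71.6% | 70.2% | 99.9% | 99.9% |

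Hand check for 100 caregivers and a half-point drift: the SD of the change is 3 × √(2 × (1 − 0.6)) = 2.68. The standardised shift is 0.5 / (2.68 / √100) = 1.86, and the approximate rejection rate is Φ(1.86 − 1.96) = Φ(−0.10) ≈ 0.46. The simulated 0.42-0.43 is a little lower, as expected with a rank test on rounded, bounded scores.

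The test is sound for the question whether burden changed: without drift it rejects in 4-5% of trials. It does not address why burden changed. The same arithmetic works in reverse: if Embrace lowered burden by half a point while background change raised it by half a point, the net change would be zero and the test would again reject only in about 5% of trials.

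**The case against.** The strongest reply is that the article never states a between-arm caregiver hypothesis. Statistical analysis treats caregivers separately, as an analysis of change. The Abstract, the aim restated under Outcome measurements and the concluding paragraph do not name caregivers. The sample size rests on elderly participants. The eligibility rule already tells a careful reader that caregivers come from one arm, and an uncontrolled caregiver substudy is legitimate. This much stands: the trial's main inference, on patient outcomes, is not touched, and the defect concerns how one outcome is labelled and what may be concluded from it. The reply does not remove the defect. The Background puts caregivers under effectiveness, CSI is called primary, Table 2 flags other intervention-group measures but not this one, and the limitations do not mention it.

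Three stronger readings are tempting, and the document does not support them.

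- A reader might infer that duration of support cannot be taken into account, because a signed-rank test has no covariate. It can be handled by testing within duration bands or by a supplementary model. An article may leave that detail to the analysis plan.
- A reader might infer a sizeable fall in CSI from regression to the mean, and set it against the 6/14 = 0.43 SD the trial is powered for. Eligibility sets no strain threshold, so selection on high scores is not shown. The 0.43 is a between-arm difference on another scale in other people.
- A reader might infer that the Wilcoxon test must give way to a regression of the T1 score. With one arm, such a model has no treatment coefficient and would not restore the missing comparison.

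**Conclusion.** The point holds as a defect in the caregiver outcome as written. CSI is a primary outcome under an effectiveness aim, yet the design gives it neither a control group nor a pre-intervention measurement. Its planned test cannot be attributed to Embrace in either direction. This rests on the article's own statements on eligibility, timing, outcome status and analysis, and on no numerical assumption.

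The size cannot be fixed from the document. Under the assumed values, with no effect of Embrace, a background drift of 0.5 to 1 CSI point gives a significant result in about 24% to over 99% of trials, depending on the number of caregivers (50 to 200). The range illustrates the risk and does not predict this trial's result. How the result will be reported is also not known. The objection is only that the text, as it stands, permits an effectiveness reading.

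**What to change.** Trial status says that follow-up is complete and analysis has not begun. Control caregivers can no longer be added, but the claim can still be settled before results are seen.

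1. In Table 2, attach the intervention-group footnote to CSI and to caregiver quality of life.
2. Reclassify caregiver burden as a descriptive, uncontrolled outcome and state that no effectiveness claim will be drawn from it. Because the change comes after data collection, record its date and reason openly.
3. In Statistical analysis, replace the term baseline for caregivers with first measurement during the intervention. Report the within-caregiver change with a 95% confidence interval, described by months between the first measurement and T1.
4. In the Discussion, add the missing caregiver control group and the missing pre-intervention caregiver measurement to the limitations.

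The cost is a change of text and table, a confidence interval in place of reliance on a p-value, and one fewer primary effectiveness claim. No new data are needed, and the analysis of patient outcomes does not change.

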*Perceived chronic illness care* will be evaluated using the Patient Assessment of Chronic Illness Care (PACIC) [51]. It reflects on all CCM elements and evaluates – from the elderly participants’ perspective – the degree to which integrated care is realized. Originally, the PACIC was developed for people with a specific chronic disease. Since the PACIC will be applied to a population of elderly persons, the disease-related items in the Dutch version of the PACIC [52] will be rephrased into questions more suitable for an ageing population.

*Self-management knowledge and behavior* will be measured with the Partners in Health scale (PIH) [53]. It assesses self-management knowledge and behavior regarding one’s chronic condition. For this study, the English PIH version will be translated into Dutch using forward and backward translation [54] and modified for the elderly population by rephrasing items.

The primary outcome regarding the *cost analysis* is the cost utility expressed in Quality Adjusted Life Years (QALYs) that will be calculated using the health status (EQ-5D) [48] and service use of participants.

*Service use* will be assessed using the Minimal Data Set-economic evaluation (MDS-e) patient self-report questionnaires. This is a set of questions evaluating a wide spectrum of services used during the previous twelve months. The questions focus on hospital stay and ER admissions, nursing-home stay, GP visits, home health care, assist devices acquired, and home adjustments. Standardized cost prices will be used to calculate the costs of services used. If possible, data will be used from databases of health insurers and municipalities.

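### The cost-utility analysis names no adjustment for T0 EQ-5D or T0 service use, although both can be taken from the T0 questionnaires; this loses precision, chiefly in the QALY difference.

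*Protocol article*

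**What the plan says.** All references are to the protocol article.

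- **Outcome.** Under Primary outcome measurements, the primary outcome of the cost analysis is "the cost utility expressed in Quality Adjusted Life Years (QALYs) that will be calculated using the health status (EQ-5D") together with service use.
- **Timing.** Data collection schedules participant questionnaires at two points, T0 and T1 at twelve months. The MDS-e asks about the preceding twelve months, so a T0 administration would cover the year before the trial.
- **Economic analysis.** Statistical analysis states "The incremental cost-effectiveness ratio will be calculated as total costs per QALY [61], and total costs per patient outcome measurement" and adds "Bootstrapping will be used to determine the confidence interval". It gives no QALY formula, bootstrap model or covariates.
- **Effect analysis.** "The first analyses will focus on the differences between intervention and control groups after intervention", at the level of the sample and of the strata, and "T-tests or (M)ANOVA will be used for continuous variables". Baseline differences between the arms are to be described.
- **Balancing.** Under Randomization, "The balancing criteria will be age, sex, complexity of care needs, frailty, living situation, number of chronic conditions, whether or not receiving homecare", plus help with the questionnaires. This is done per stratum within each practice. EQ-5D and total cost are not on the list.
- **Status.** Follow-up is complete and data analysis has not begun (Trial status).

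**The concern.** A QALY over twelve months built from two EQ-5D measurements normally contains the T0 measurement. This goes beyond leaving T0 out of a test on T1 scores: the T0 value is part of the outcome itself. Whatever difference in starting utility chance leaves between the arms then passes into the incremental QALY, though Embrace cannot have caused it. The bootstrap interval also carries between-person variation that a known covariate would remove. Costs have a milder form of the same problem, because prior-year service use usually predicts later use. The stake is a less precise answer on cost utility than the collected data can give.

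**Working it through.** **1. The plan's own size.** Inputs from Sample size: difference 6, SD 14, two-sided 0.05, power 80%. Then n = 2 × [14 × (1.960 + 0.842)/6]² = 85.47. The stated 85 therefore reproduces as a number per arm (power 79.8%). With stratum B at 16%, 30% non-response and 30% loss, the number invited is 2 × 85.47/0.16/0.7/0.7 = 2180, against 2178 stated. I use 85 per arm for the smallest stratum. For the whole sample, 2178 × 0.7 × 0.7 = 1067 completers, or about 534 per arm.

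**2. QALY as area under the curve.** Assumptions not in the article: QALY = (U0 + U1)/2, equal SD s at T0 and T1, and T0-T1 correlation ρ.

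- Unadjusted variance: s²(1 + ρ)/2
- Variance given U0: s²(1 − ρ²)/4
- Width ratio, unadjusted to adjusted: √[2/(1 − ρ)]
- Share of a T0 difference that enters the QALY difference: (1 + ρ)/2

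| ρ | QALY width ratio | Share carried over |
|---|---|---|
| 0.3 | 1.69 | 0.65 |
| 0.5 | 2.00 | 0.75 |
| 0.7 | 2.58 | 0.85 |

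A simulation at ρ = 0.5 with 85 per arm gave a ratio of 2.0.

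**3. QALY as change from T0.** If instead QALY = (U1 − U0)/2, the unadjusted variance is s²(1 − ρ)/2 and the width ratio is √[2/(1 + ρ)]: 1.24, 1.15 and 1.08 at ρ = 0.3, 0.5 and 0.7.

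**4. Costs.** With correlation ρc between T0 and follow-up cost, the width ratio is 1/√(1 − ρc²): 1.05, 1.15 and 1.40 at ρc = 0.3, 0.5 and 0.7.

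**5. Joint result.** I use net benefit as a stand-in for the ratio, with area-under-the-curve QALYs. Purely illustrative assumptions: utility SD 0.25, cost SD 5,000 to 20,000, value per QALY 20,000 to 80,000, ρ 0.5 to 0.7, ρc 0.3 to 0.5, costs and QALYs uncorrelated. The width ratio runs from 1.07 to 2.29 and is below 2 in 25 of the 27 combinations tried.

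**6. Power for the QALY difference.** This applies the VAS standardised difference 6/14 = 0.43 to T1 utility (an assumption), so the QALY effect is 0.214 s under the formula in step 2.

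| ρ | 85 per arm, unadjusted | 85 per arm, adjusted | 534 per arm, unadjusted |
|---|---|---|---|
| 0.3 | 41% | 83% | 99% |
| 0.5 | 36% | 90% | 98% |
| 0.7 | 33% | 97% | 97% |

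The gain is large within the smallest stratum. In the whole sample it is under 4 points.

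**7. Chance imbalance at ρ = 0.5, before any effect of balancing.** With 85 per arm, one standard error of the T0 difference is √(2/85) = 0.153 s. It moves the QALY difference by 0.75 × 0.153 = 0.115 s, or 54% of 0.214 s. With 534 per arm it is 0.75 × √(2/534) = 0.046 s, or 21%.

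**8. Balancing.** If balancing on related characteristics removes 30% to 70% of the chance T0 utility variance between arms (assumed), the true standard-error ratio at ρ = 0.5 falls from 2.0 to between 1.76 and 1.38. A bootstrap that ignores both the balancing and T0 would still report the wider interval.

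**The case against.** The strongest reply is that the article is silent and does not commit to an unadjusted comparison. The economic analysis takes three sentences, no covariate is ruled out, the Discussion lists control for confounders among the design's features, and a fuller plan may name the model. This stands to the extent that a reader should not infer that the investigators have chosen to leave T0 out. However, the Discussion gives no method, and the methods the article does name for continuous effect outcomes are unadjusted. Fixing the adjustment in advance is useful either way.

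A reader might also infer that the cost-utility interval is about twice as wide as it need be. The documents do not support that. A factor of two needs ρ = 0.5 and the (U0 + U1)/2 formula, neither of which is given, and it describes the QALY difference, not the joint cost and QALY result.

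Nor do the documents support reading this as bias that could make Embrace look cost-effective because one arm started healthier. Allocation is randomized, and balancing on complexity, frailty, chronic conditions and homecare should reduce T0 differences further. If balancing works well, an unadjusted interval is too wide, which errs on the cautious side.

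The stratum-level power figures also need care. The article does not say expressly that a cost-effectiveness ratio will be given per stratum, although effects are analysed at that level and Table 2 lists EQ-5D and MDS-e as primary in every stratum.

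Finally, MDS-e at T0 is inferred from the data-collection schedule, not stated outright, and outcome costs may come from insurer and municipal records. That part of the objection stands and shapes the choice of cost covariate.

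**Conclusion.** The point holds as an inexpensive improvement to the primary cost-utility analysis, not as an error that invalidates it. The analysis as described names no baseline adjustment although baseline values can be had. Under area-under-the-curve QALYs, the unadjusted QALY-difference interval is about 1.7 to 2.6 times as wide as the adjusted one for ρ from 0.3 to 0.7. Under change-from-T0 QALYs it is 1.1 to 1.2 times. For costs the factor is about 1.05 to 1.4, so the joint interval gains less than QALYs alone. The correlations, the QALY formula and the equal SDs are my assumptions. The consequence is lost precision and exposure to chance imbalance. It matters most for any stratum-level result, since whole-sample power for the QALY difference is already about 97% to 99% under the plan's own size and effect assumptions.

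**What to change.** Before data analysis starts, state the QALY formula and specify the following:

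- The incremental QALY is estimated by regression of QALY on arm and T0 EQ-5D utility.
- The incremental cost is estimated by regression of cost on arm and T0 service-use cost. Use T0 MDS-e cost, or pre-trial records if outcome costs come from insurer and municipal records.
- Stratum is a covariate in both whole-sample models.
- Both regressions are fitted within each bootstrap replicate, so that the ratio and its interval rest on the adjusted differences.

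The cost is a short addition to the plan and two regressions per replicate. No new participant questionnaires are needed. The one downside is that some T0 items will be missing, so a rule for handling them should be set at the same time. Fixing this now also avoids the adjustment being chosen after an imbalance has been seen.
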